## Abstract

Type 2 diabetes mellitus has a worldwide prevalence of 10.5% in the adult population (20–79 years), and by 2045, the prevalence is expected to keep rising to one in eight adults living with diabetes. Mild cognitive impairment has a global prevalence of 19.7% in adults aged 50 years. Both conditions have shown a concerning increase in prevalence rates over the past 10 years, highlighting a growing public health challenge. Future forecasts indicate that the prevalence of dementia (no estimations done for individuals with mild cognitive impairment) is expected to nearly triple by 2050. Type 2 diabetes mellitus is a risk factor for the development of cognitive impairment, and such impairment increase the likelihood of poor glycemic/metabolic control. High phytate intake has been shown to be a protective factor against the development of cognitive impairment in observational studies. Diary phytate intake might reduce the micro- and macrovascular complications of patients with type 2 diabetes mellitus through different mechanisms. We describe the protocol of the first trial (the PHYND trial) that evaluate the effect of daily phytate supplementation over 56 weeks with a two-arm double-blind placebo-controlled study on the progression of mild cognitive impairment, cerebral iron deposition, and retinal involvement in patients with type 2 diabetes mellitus. Our hypothesis proposes that phytate, by inhibiting advanced glycation end product formation and chelating transition metals, will improve cognitive function and attenuate the progression from Mild Cognitive Impairment to dementia in individuals with type 2 diabetes mellitus and mild cognitive impairment. Additionally, we predict that phytate will reduce iron accumulation in the central nervous system, mitigate neurodegenerative changes in both the central nervous system and retina, and induce alterations in biochemical markers associated with neurodegeneration.

## Introduction

1

The treatment and prevention of increasing numbers of patients with type 2 diabetes mellitus (T2DM) and mild cognitive impairment (MCI) due to demographic and lifestyle changes are important challenges faced by healthcare systems. MCI is a milder form of cognitive dysfunction that precedes dementia and affects almost one in two people over the age of 65 with T2DM (1). People with MCI are at high risk of dementia (DE); the majority of studies indicate a progression rate to DE ranging from 20% to 40%, with an annual rate ranging between 5% and 17% (2). In addition, people with T2DM have a very high risk of MCI in comparation to the non-diabetic population. In these sense, it has been recognized that T2DM acts as an important accelerator of DE in patients with MCI (3, 4). Cognitive impairment makes self-care difficult and increases the risk of hypoglycemia, which increases comorbidity, hospital admissions, and the costs of T2DM to healthcare systems (5, 6).

T2DM has been correlated with an accelerated decline in cognitive function among the elderly and an increased likelihood of developing mild cognitive impairment and a higher risk of dementia, including both Alzheimer’s disease (AD) and vascular dementia (7). In fact, T2DM doubles the risk of developing AD. This increase is maintained even after adjusting for vascular risk factors (8, 9). The mechanism connecting diabetes to AD is multifactorial and not well-defined. However, its pathogenesis is known to involve a decrease in brain-derived neurotrophic factor (BDNF) and an increase in oxidative stress due to the accumulation of advanced non-enzymatic glycation products (AGEs), systemic inflammation via tumor necrosis alpha (TNF-a), interleukin 1beta (IL-1b) and interleukin 6 (IL-6), increased lipid peroxidation, and decreased superoxide dismutase (SOD) activity (7, 10). In AD, it has been seen that AGEs, through their receptor (RAGE), increase the expression of tau and Aß (11).

Concomitantly, people with T2DM have a higher prevalence of sarcopenia and dynapenia in comparison with an age-matched population without T2DM. This prevalence could be a consequence of chronic inflammation and oxidative stress associated with this condition (12). In addition, sarcopenia and dynapenia have been associated with cognitive impairment (13). The preservation of the muscle tissue could be an effective strategy for improving not only metabolic state but also cognitive performance.

Investigating the relationship between iron homeostasis and mild cognitive impairment (MCI) is pivotal, considering the emerging evidence suggesting a potential link between disrupted iron metabolism and cognitive decline. Iron plays a crucial role in various cellular processes, including oxygen transport, energy metabolism, and neurotransmitter synthesis. However, dysregulation of iron homeostasis can lead to the accumulation of excess iron in the brain, contributing to oxidative stress, neuroinflammation, and neuronal damage (14). Ferroptosis is a unique form of iron-mediated programmed cell, which is distinct from apoptosis, necrosis, autophagy, and other forms of cell death (14). Iron deposits in neurons are closely tied to neurodegeneration and cognitive decline, although the specific mechanisms driving these connections remain uncertain (14). Various factors can alter iron homeostasis, causing the gradual accumulation of iron in various tissues, including the central nervous system (CNS) (15–17). Aging itself and diseases such as AD, Parkinson’s disease, and Huntington’s disease, among others, are related to an increase in iron levels in the region of the brain affected. The level of iron accumulation also correlates with the severity of the disease (18, 19). In addition, iron overload is associated with age-related macular degeneration and a subset of psychiatric diseases (20, 21).

Ferroptosis plays a role in neuronal loss during acute or chronic brain injury, and blocking ferroptosis could decrease cell death and improve neurological function in animal models (22). Conservative iron chelation has been proposed as a new therapeutic concept for the treatment of neurodegenerative diseases associated with increased iron storage (21). Unlike the chelators used for the treatment of systemic diseases, these chelators need to cross the blood–brain barrier (BBB). Deferoxamine, a hexadentate ligand with high affinity for Fe(III), is capable of inhibiting amyloid formation *in vitro (*
23). However, it has difficulty in crossing the BBB when administered orally and also has side effects (24, 25). Clioquinol, a lipophilic binder, has been used successfully in phase II trials in moderate AD, but it is not iron selective and has significant side effects (26). Bearing this in mind, developing a chelator for treating neurodegenerative diseases, especially in individuals with MCI and T2DM, which is effective, easy to administer, and free of side effects, presents a considerable challenge.

Phytate (myo-inositol hexaphosphate, IP6) is a natural compound present in seeds (e.g., cereals, legumes, and nuts) as a calcium–magnesium salt (phytin) (27, 28). It possesses the ability to chelate various divalent and trivalent cations, including iron (27, 29–31) with a higher affinity than commonly used chelating agents like EDTA, deferoxamine, or deferiprone (30). This suggests that the consumption of IP6 could reduce iron bioavailability, and IP6 is able to cross de BBB (28, 32, 33). Moreover, in a study where we evaluated the relationship between dietary phytate (34), mineral status, and phytate levels in the body, it was observed that the amount of iron found in the brains of rats fed phytate diets was significantly lower than that found in rats fed non-phytate diets. Recently, an observational study has reflected that phytate intake was positively associated with cognitive function (35). Our group has shown that IP6 prevents the formation of pathological calcifications *in vivo*, such as calcium kidney stones (36, 37), sialolithiasis (38), and vascular calcification (39, 40), and protects against osteoporosis (41). In animals and cell models, phytate could also provide protection against cancer (33) and Parkinson disease (42). In a recent clinical trial with high safety levels, we have shown that daily phytate intake for 3 months is capable of reducing the levels of advanced glycation end products in T2DM patients (40). To our knowledge, no randomized clinical trial with IP6 supplementation and cognitive impairment have been carried out so far.

Our hypothesis is that phytate, due to its ability to inhibit the formation of AGEs and to chelate transition metals, will improve cognitive ability and delay the progression of mild cognitive impairment to dementia in patients with T2DM and MCI. It will also slow/prevent/mitigate the accumulation of iron in the CNS and the changes associated with neurodegeneration both in the CNS and in the retina. Likewise, changes in the biochemical markers associated with neurodegeneration are to be expected.

## Objectives

2

### Main aims

2.1

The main aims of this study are as follows:

To evaluate the effect of daily phytate intake on cognitive ability and compare it with the placebo group.To determine the effect of daily phytate intake on morphological changes and iron storage associated with cognitive impairment in diabetes by magnetic resonance imaging (MRI).

### Secondary aims

2.2

The secondary aims of this study are as follows:

To evaluate the effect of daily phytate intake on the evolution of retinal neurodegeneration parameters and diabetic retinopathy.To determine the effect of daily phytate intake on the evolution of plasmatic biomarkers associated with cognitive decline and aging.To assess the effect of daily phytate intake on body composition (using bioimpedance vector and muscle ultrasound) and grip strength (by dynamometry).

## Experimental design

3

### Design

3.1

The PHYND trial is a two-arm, double-blind, placebo-controlled study designed to evaluate the effect of daily phytate supplementation on the progression of mild cognitive impairment, brain iron storage, and retinal involvement in patients with type 2 diabetes. Patients diagnosed with MCI, and whose consumption of phytates is in the low/moderate range, will be recruited by the Endocrinology and Nutrition Service of the Son Llátzer University Hospital. The treatment will be diet modification: Arm 1 will take capsules of phytate dietary supplement three times a day (in the form of Lit-Control pH Balance) compared to Arm 2, which will take placebo capsules three times a day.

The present protocol was elaborated following the Standard Protocol Items: Recommendations for Intervention Trials (SPIRIT) 2013 Statement (43). Reporting of the study will follow the CONSORT statement recommendations on RCTs (44). **Table 1** summarizes all items included in the trial registry, as suggested by the World Health Organization (WHO, 2018) (45).

**Table 1 T1:** Data collection by visits.

	Initial evaluation	Initial evaluation	Start	Continuation visit	Continuation visit	Continuation visit	Continuation visit	Last visit	Follow-up
*Weeks number*	−8	−4	0	4	14	28	42	56	65
*Informed consent*									
*Inclusion & Exclusion criteria*									
*Questions about health and disease*									
*Physical examination*									
*Blood pressure and heart rate measurement*									
*ApoE genotype*									
*LUES serology*									
*Food frequency questionnaire*									
*Medical history evaluation*									
*Grip Strength*									
*MOCA questionnaire*									
*SAGE questionnaire*									
*Magnetic Resonance Imaging*									
*Ophthalmologic evaluation*									
*Beck questionnaire*									
*Rey figure*									
*Pittsburg Sleep Quality Index*									
*2-h urinary phytate determination*									
*Body composition evaluation*									
*Lab test*									
*AD biomarkers determination (TNF-alpha, IL-1B, IL-6, NF, t-tau, p-tau 181, Ab-42, Ab-40)*									
*AGE and RAGE determination*									
*Adverse effect evaluation*									
*Pill counting*									

### Baseline variables

3.2

Variables to be measured to evaluate inclusion criteria are the following:

Diagnosis of MCI: cognitive screening for MCI will be performed using the Montreal Cognitive Assessment Test (MoCA) and the Self-Administered Gerocognitive Test (SAGE). We stratified MoCA results by race/ethnicity and education level before applying a cutoff value for the MoCA score to achieve more accurate cutoffs as suggested by Milani et al. (2018). “Mild cognitive impairment” will be considered when SAGE<17 (46) and MoCA-adjusted score (47) corresponds to an MCI.Neuropsychological test (NPT): in patients who score MoCA corresponds to a MCI considering race and years of education, a cognitive assessment will be carried out using the following neuropsychological tests (NPT): SAGE, digit and symbol substitution test (DSST), line test in version A and B (TMT-A and TMT-B), Rey Auditory-Verbal Learning Test (RAVLT), Rey–Osterrieth Complex Figure Copy and Recall (ROCF), Boston Naming Test (BNT), and phonetic and semantic verbal fluency will also be tested. Through these tests, we will examine the following domains: visual scanning and processing speed (DSST, TMT-A), divided attention and executive function (TMT-B and verbal fluency), learning, retention memory and verbal recall (RAVLT), constructive praxia (including motor skills), visual memory (ROCF), and language (BNT). All these tests are validated in Spanish language. NPTs will not be performed unless the diagnosis of MCI with MoCA is established.Phytate dietary questionnaire: a score ≤5 will be considered low/moderate phytate consumption (48).Apolipoprotein E (APOE) genotype in serum samples.

### Participants

3.3

#### 
Inclusion criteria

3.3.1

Those aged over 60 years, with a diagnosis of mild cognitive impairment, according to the MoCA and SAGE, low/moderate phytate intake, T2DM evolution of over 5 years, no history of cerebrovascular accident or neurodegenerative disease, no acute myocardial infarction or heart failure during the previous 6 months, no severe pre-proliferative retinopathy or proliferative retinopathy, and those who have signed the informed consent will be included.

#### 
Exclusion criteria

3.3.2

Those with illnesses or disorders that could affect deterioration, safety or adherence, immuno-suppressants, epilepsy, neoplasia in the previous 5 years, alcohol or drug abuse, anti-Parkinsonian or anticonvulsant medication, iron metabolism pathologies such as hemochromatosis and blood disorders requiring transfusions, skin neoplasia (history of cancer during the 5 years prior to the day of screening) with the exceptions of basal cell and squamous cell carcinoma of the skin and any carcinoma *in situ*, and those who are participating in any another clinical trial will be excluded.

#### 
*Patient withdrawal criteria*

3.3.3

The investigator must withdraw patients from the study when at least one of the following circumstances occurs: death, withdrawal of informed consent, and loss to follow-up. The reason and date of withdrawal from the study must be included in the Data Collection Notebook (DCN).

### Sample calculation and randomization

3.4

There are no data on the effects of phytate supplementation on mild cognitive impairment. The sample size has been calculated based on other dietary intervention studies on MCI considering an alpha risk of 0.05 and a statistical power of 0.8 (49). Bearing in mind that we anticipate that there will be a difference of 30% in the progression of cognitive deterioration between those assigned diet 1 and those assigned diet 2, for a bilateral hypothesis test, a power of 80%, an alpha of 0.05, and a percentage of losses of 15%, we would obtain a minimum sample of 45 T2DM patients. Randomization will be 1:1 using fixed size stratified blocks. The stratification factors will be APOE genotype, age (75 years), gender, duration of diabetes (10 years), and previous cardiovascular disease (50).

## Procedure

4

### Description of interventions

4.1

Patients will have nine visits between week −8 (−8) and week 56 (w56), with week 0 (w0) being the point of randomization and start of treatment. These visits will take place in the endocrinology service of the Son Llàtzer University Hospital. **Figure 1** sums up the different interventions that will take place in each visit. Furthermore, a follow-up visit will be performed at week 62 (w62).

**Figure 1 f1:**
[figure not shown]
Outlines the actions to be conducted in each visit.

#### Visit 1 (week −8)

4.1.1

At the patients’ first visit (v1, w-8), inclusion criteria will be reviewed to ensure that they are eligible. To verify that the patient meets all the criteria deemed necessary to participate, the following procedures will be carried out:

- They will be informed about the different aspects of the study and given the information sheet so that they can read it carefully.- They will be asked to read and sign the informed consent document.- Questions about health and disease will be carried out.- They will be asked questions about their medical history, and the researcher will check with them if they meet the requirements to participate in the project, including asking questions about their eating habits, consumption of tobacco, alcohol, and other substances.- They will undergo screening tests for cognitive impairment and do the phytate dietary survey.- A hand grip strength dynamometry will be performed to measure the grip strength in the dominant and contralateral hand.- They will be asked if they are taking any other medication at the time of the project.- The doctor will perform a complete physical examination, including taking height and weight measurements, to check their general state of health.- Determination of APOE genotype and LUES serology will be requested.- Their vital signs will be measured, including heart rate, blood pressure, and body temperature.- They will be given a 2-h urine collection container to use for the next visit, and they will be scheduled for a baseline test at week −4.

#### Visit 2 (week −4)

4.1.2

On this visit:

- Questions about health and disease will be carried out.- They will be asked if they are taking any other medication at the time of the project.- Their vital signs will be measured, including heart rate, blood pressure, and body temperature.- The relevant neuropsychological tests will be completed.- They will be scheduled for a non-contrast MRI and ophthalmological tests to take place between week −4 and week 0.

#### Visit 3 (week 0)

4.1.3

In the case of patients who meet all the inclusion criteria and none of the exclusion criteria, the corresponding variables of the clinical history will be recorded in the DCN. On this visit:

- Questions about health and disease will be carried out.- They will be asked if they are taking any other medication at the time of the project.- The doctor will perform a complete physical examination, including taking height and weight measurements, to check their general state of health.- Their vital signs will be measured, including heart rate, blood pressure, and body temperature.- Body composition assessment will be carried out using vectorial bio-impedance analysis (BIA) and Nutritional Ultrasound to measure the diameter of the rectus femoris of the quadriceps and preperitoneal visceral adipose tissue (51).- Non-contrast MRI and ophthalmological tests will take place between week −4 and week 0.- Pittsburg Sleep Quality Index will be administered (52).

These patients will be randomly assigned to one of two treatment arms:

- Arm 1: 56 weeks with phytate dietary supplement- Arm 2: 56 weeks with placebo

Diets will consist of:

*-* Treatment with phytate: patients will continue with their usual diets (low/moderate in phytate), and in addition, they will ingest three capsules a day (breakfast, lunch, and dinner) of a dietary supplement of 300 mg/sachet of phytate (in the form of phytin) over the course of 56 weeks. The doctor will give them the correct number of capsules to last until the next visit. At the next visit, a blood test will be requested (in line with usual clinical practice), and a 2-h urine sample will be collected again to determine the urinary phytate concentration at weeks 0, 28, and 56.
*-* Placebo treatment: patients will continue with their usual diets (low/moderate in phytate) and, in addition, will ingest three placebo capsules a day (breakfast, lunch, and dinner) over the course of 56 weeks. The doctor will give them the correct number of capsules to last until the next visit. At the next visit, a blood test will be requested (in line with usual clinical practice), and a 2-h urine will be collected again to determine the urinary phytate concentration at weeks 0, 28, and 56.

#### Visits 4 (week 4), 5 (week 14), 6 (week 28), and 7 (week 42)

4.1.4

On these visits:

- Questions about health and disease will be carried out.- They will be asked if they are taking any other medication at the time of the project.- Safety will be reviewed. Any of the following outcomes will be recorded as serious adverse events: death, hospitalization of more than 24 h, persistent disability, and any other results that endanger the life of the subject. Episodes of clinically significant iron deficiency or anemia and episodes of hypoglycemia <54 mg/dl and level III hypoglycemia (that is, requiring the assistance of a third party) will be collected with particular interest.- The doctor will perform a complete physical examination, including taking height and weight measurements, to check their general state of health at weeks 0 and 28.- Their vital signs will be measured, including heart rate, blood pressure, and body temperature.- At week 28, a urine sample will be collected.- At weeks 14, 28, and 42, blood tests will be performed.- Patients will be given a dietary survey to assess their adherence to the low phytate diet.- Remaining supplement capsules will be collected and counted, and the correct number of capsules will be given to last until the next visit.- Patients will be given a 2-h urine collection container that must be brought to their next visit at week 28.- The final visit will be scheduled, where a blood test will be performed in line with usual clinical practice.

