#### Visit 8 (week 56)

4.1.5

At this end-of-treatment visit:

- Safety will be reviewed, as above.- Neuropsychological and cognitive deterioration tests will be completed again.- Urine samples will be collected, and a blood test will be performed.- A dietary survey to assess patient adherence to the low phytate diet will be completed.- Any surplus supplement capsules will be collected, counted, and accounted for.- The doctor will perform a complete physical examination, including taking height and weight measurements, to check the patient’s general state of health.- Vital signs will be measured, including heart rate, blood pressure, and body temperature.- A non-contrast MRI and ophthalmological tests will be performed this week.- Body composition assessment will be carried out using vectorial BIA and Nutritional Ultrasound to measure the diameter of the rectus femoris of the quadriceps and preperitoneal visceral adipose tissue (51).- Pittsburg Sleep Quality Index will be administered.

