## Safety

6

The treatment that is used, Lit-Control^®^ pH Balance, has been developed with ingredients that have been internationally recognized as safe. No incidents have been reported by its consumers since the beginning of its commercialization on said date. However, in case that a possible serious adverse event was to be detected and recorded, the treatment would be suspended and the investigator would proceed as follows:

- The sponsor would be immediately informed of all adverse events. Immediate notification must be followed by timely detailed written reports. The immediate and follow-up report must identify subjects by a unique code assigned to the trial subject and not by the subject’s name, personal identification numbers, or subject’s address. The investigator must also comply with the legal regulations regarding the notification of serious and unexpected adverse events to the relevant authorities and to the CEI-IB.- When the researcher notifies a death, he must provide the promoter and the CEI-IB with all the complementary information that they request (e.g., the autopsy report and the most recent medical reports). An adverse event (AE) will be considered any adverse health incident that occurs in a patient who has received a treatment, even where there is not necessarily a causal relationship with said treatment. An adverse event (AE) can therefore be any unfavorable and unintended sign (including an abnormal laboratory finding), symptom, or disease temporarily associated with the use of treatment, whether or not related to it.

According to current regulations, “serious adverse events” will be considered as “any adverse reaction that causes death, may be life-threatening, requires hospitalization of the patient or prolongation of existing hospitalization, causes significant or persistent disability or invalidity, or constitutes a congenital anomaly or birth defect. Those suspected adverse reactions that are considered important from a medical point of view, even if they do not meet the above criteria, such as those that put the patient at risk, or require intervention to prevent any of the above outcomes, will also be treated as serious, as will all suspicions of transmission of an infectious agent through a medication (RD 1090/2015, art. 22.1.d “Serious adverse reaction”)”.

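### Sections 4.1.4 and 6 define a serious adverse event differently, and even read together they class some unrelated serious events as non-serious.

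*Protocol article*

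**What the plan says.** Section 4.1.4 of the protocol article (visits at weeks 4, 14, 28 and 42) tells staff what to record: "Any of the following outcomes will be recorded as serious adverse events: death, hospitalization of more than 24 h, persistent disability", together with "any other results that endanger the life of the subject". The end-of-treatment visit uses the same list: "Safety will be reviewed, as above" (section 4.1.5).

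Section 6 (Safety) gives a second definition under the same label. A serious adverse event is "any adverse reaction that causes death, may be life-threatening, requires hospitalization of the patient or prolongation of existing hospitalization". The list continues with significant or persistent disability and congenital anomaly. It then adds "Those suspected adverse reactions that are considered important from a medical point of view" and suspected transmission of an infectious agent. The text is attributed to a Spanish royal decree, under that decree's heading for a serious adverse reaction.

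Just before this, section 6 defines an adverse event as any unfavourable occurrence in a treated patient, related to treatment or not.

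Three further statements in section 6 use these terms:

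- On treatment: "in case that a possible serious adverse event was to be detected and recorded, the treatment would be suspended".
- On reporting to the sponsor: "The sponsor would be immediately informed of all adverse events".
- On outside notification: "The investigator must also comply with the legal regulations regarding the notification of serious and unexpected adverse events".

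**The concern.** A serious adverse event is normally an adverse event that meets one of the seriousness criteria, with relatedness judged separately. Here the two definitions differ on both dimensions. Section 4.1.4 ignores relatedness but has the narrower criteria. Section 6 has the wider criteria but, read literally, admits only reactions. The move from *event* to *reaction* happens inside section 6, a few lines after it has said that an adverse event needs no causal link.

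What is at stake is the safety classification. Participants are over 60 with more than five years of diabetes, so short admissions and complications unrelated to the supplement are plausible. Whether such an event appears in the trial's serious-event table should not depend on which section the person filling in the form has read.

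**Working it through.** The point rests on no sample size, power or alpha figure, and the article gives no event rates, so no arithmetic applies. The check sets the two definitions side by side and classifies each type of event under each one, and then under both together (serious if either section says so).

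Inputs: the list in section 4.1.4, carried to week 56 by section 4.1.5, and the list in section 6, with *reaction* taken literally as at least a suspected causal link.

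| Event | Relation to treatment | Serious under 4.1.4 | Serious under 6 | Serious under either |
|---|---|---|---|---|
| Death, life-endangering result or persistent disability | suspected | yes | yes | yes |
| Same | unrelated | yes | no | yes |
| Admission over 24 h | suspected | yes | yes | yes |
| Same | unrelated | yes | no | yes |
| Admission of 24 h or less | suspected | no | yes | yes |
| Same | unrelated | no | no | **no** |
| Prolongation of an existing stay, by itself | suspected | no | yes | yes |
| Same | unrelated | no | no | **no** |
| Medically important, not life-endangering | suspected | no | yes | yes |
| Same | unrelated | no | no | **no** |

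Step 1. The definitions differ in both directions. A suspected reaction with a 20 h admission is serious under section 6 only. An unrelated three-day admission is serious under section 4.1.4 only. Neither list is a shortened form of the other.

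Step 2. Section 4.1.4 does not claim to be exhaustive, so the generous reading applies both lists. That removes every disagreement in the table except the three bold rows, where an unrelated event meets neither list.

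Step 3. Congenital anomaly follows the same pattern, since only section 6 names it and only as a reaction. It has little practical weight in participants over 60.

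Step 4. One example concerns an event the trial itself wants watched. Suppose a participant needs another person's help for severe hypoglycaemia, is treated within 24 h, and the episode is attributed to glucose-lowering medication. Section 4.1.4 singles out such episodes for collection. By the two lists, however, the episode is serious under neither section unless someone judges that it endangered life.

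**The case against.** The strongest reply is that little is lost. Section 4.1.4 can be read together with section 6, so unrelated deaths, life-endangering results, persistent disability and admissions over 24 h are recorded as serious whatever section 6 says. The sponsor hears of all adverse events, legal notification rules apply separately, and iron deficiency, anaemia and hypoglycaemia are collected in any case. All of this stands. It confines the defect to the three bold rows and makes it one of classification. A reader might infer that events go unreported or that the arms would be biased. The documents do not support the first, because of the reporting duty just described. Nor do they show the second, since the arms are blinded and the same definitions apply to both.

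A second reply is that a journal article condenses a fuller protocol. That excuses omissions, but here two rules are stated and they differ. A 24 h threshold that appears in one place only does not abbreviate a rule without one.

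A reader might also go further and infer that the suspension rule leaves it open whether an event must be related, so that treated time depends on which section is followed. The text does not support this. The rule speaks of a *possible* serious adverse event and sets no relatedness condition. Section 6's own definition of an adverse event is causality-free, as is section 4.1.4. The natural reading is that a serious event suspends treatment whether or not it is related. Any estimate of capsule time lost would need an admission rate and an assumption that suspended treatment is never restarted, and the article gives neither. Limiting suspension to related events would be a policy choice, and the broader, more cautious rule is not an error.

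**Conclusion.** The inconsistency is real and comes from the stated text. Section 4.1.4 is causality-free with narrow criteria. Section 6 has wide criteria but borrows a reaction definition and so contradicts its own definition of an adverse event. On the reading most favourable to the protocol, unrelated admissions of 24 h or less, unrelated prolongations of a stay and unrelated medically important events that do not endanger life are still classed as non-serious. If section 6 alone were applied, all unrelated events would drop out. That is possible, but it is not the fairest reading of the two sections together.

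The size cannot be put as a number because the article gives no event rates. The direction is clear: serious events would be under-classified. The conclusion assumes that *reaction* carries its usual meaning of a suspected causal link, which the cited heading supports. No effect on the primary outcomes, the error rate or power is shown or claimed. The point is worth correcting because it concerns safety reporting and the change is cheap.

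**What to change.** Use one definition in both sections, independent of causality: death; a life-threatening event; any inpatient hospitalisation or prolongation of one; persistent or significant disability; congenital anomaly; or a medically important event. Drop the 24 h limit from section 4.1.4. Record the relatedness judgement as a separate item on the adverse event form, and keep the term serious adverse reaction for the related subset, which is where the decree's wording belongs. Have the suspension rule in section 6 refer to this single definition.

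The cost is rewording in two sections and one form field. The downside is that slightly more events will be labelled serious. Because the suspension rule refers to serious events, those additional events would fall under it too.
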